#### Qualitative

The maximum target sample for the qualitative studies is as follows: *n* = 40 parents, *n* = 40 children, and *n* = 40 group leaders. The sample recruitment will cease when data saturation is reached, that is when additional interviews fail to provide novel information. The parents and children recruited for the qualitative study will be selected from a sub-set of the entire sample for the study (i.e., *N* = 360) based on their consent to be interviewed.

## Recruitment {15}

### Recruitment of municipalities

Recruitment of families will be conducted at the municipality level. Recruitment of municipalities began in 2019 with written invitations and information meetings which was held by the research staff in different sites all over Norway. An invitation letter was sent to the child and family services and immigrant services via the study coordinator, group leaders or Bufetat. The invitation letter described study aims, project participation, and both interventions. The recruitment process will be ongoing throughout the project period until the target of *N* = 360 families is reached

### Recruitment of families

Municipalities will identify and make initial contact with families who meet eligibility criteria. Each participating municipality, or site, is given some freedom for how they will make contact with eligible families. Some municipalities may opt to invite families to a meeting to learn about the study. Other families may be approached individually and recruited thusly.

#### Informed consent from participants

Families will be considered “recruited” when they have (A) returned a signed consent form electronically or via mail or (B) have submitted contact information electronically. In the latter case, these families’ data will be held only as long as it reasonably takes to receive a written consent. If no written consent is forthcoming, attempts will be made to contact these families to secure consent, but in the even that it is not possible, their data will be deleted, and a note will be made explaining the reason for our records. In the informed consent answered by parents, they will indicate whether their child can be contacted for an interview. In the event that the child may be contacted and agrees to the interview, recorded, verbal consent will be obtained by the researcher at the beginning of the interview. A copy of the information letter and consent form can be requested by email at: [contact]

#### Recruitment of group leaders

Group leaders are identified by municipalities and the implementation teams of IY and ICDP. If the group leaders require training, they will be trained by the implementation teams.

## Assignment of interventions: allocation

### Sequence generation {16a}

A project analyst at the primary site who does not have contact with sites or families will do the allocation of the factorial conditions using a random number sequence where groups at each site are assigned an ID and then each ID is assigned either to condition 1 (w/MFS) or 0 (no-MFS) (stage 1 randomization). A second list of IDs representing families is also randomized (stage 2) to condition 1 (IY) or 2 (ICDP). To understand the randomization, it is important to understand that each site will conduct both an IY and ICDP parenting group concurrently, so that families can be randomly assigned to either group. However, sites are not capable of running four unique groups concurrently (i.e., IY w/MFS, IY no-MFS, ICDP w/MFS, ICDP no-MFS). Therefore, randomization occurs in two stages. Stage 1 randomly assigns the two groups at each site to the MFS condition (factor 2). For example, at site 1, the IY group is randomly assigned to the MFS condition, and the ICDP group is assigned to the no-MFS condition. The decision to randomize the MFS condition at the group level is practical: in order to use the MFS properly, the group leaders need to respond to the feedback. Therefore, any actions taken by the group leader will affect the entire group. In order to minimize systematic differences that may be introduced by group leaders, the groups will be re-randomized to the MFS condition when a new group begins, or roughly once per semester.

Stage 2 randomization is responsible for assigning families at each site to one of the two parenting conditions (i.e., IY or ICDP; factor 1). Stage 2 randomization by the primary site will occur after the T1 survey has been completed by the participating families.

### Concealment mechanism {16b}

Families, group leaders, and implementation teams will be unaware of their treatment condition until after they have completed the T1 survey.

### Implementation {16c}

To preserve the factorial design, we need to randomize to four conditions (see table in the “Trial Design” section of this document). We cannot randomize families to four separate conditions at each site, because this would require running four groups at each site every semester (see also the “Sequence generation {16a}” section). It would not be feasible for the municipalities to conduct four groups in parallel due to the staffing requirements. Therefore, randomization in PIRM has two stages: stage 1, randomization to MFS condition at the group level, and stage 2, randomization of families to IY or ICDP parenting groups.

Recruitment of families at each site will be ongoing. Families will be randomized when (a) a maximum of 12 families are recruited or (b) a cutoff date is reached each semester. The cutoff date will be established by the amount of time it takes to complete a group, (i.e., 15 weeks for IY, 12 weeks for ICDP). In Norway, summer holidays usually occur between June and August; therefore, groups must have adequate time to finish within the time period from January to June or late August to December.

The parenting groups (2 per site) are randomly assigned to one of the MFS (Y/N) conditions so that one group at each site will be in the MFS conditions. For example, at site 1, the ICDP group is randomly assigned to the MFS condition during the first semester. The following semester the groups will be reassigned and the IY group at site 1 may end up in the MFS condition.

## Assignment of interventions: blinding

### Who will be blinded {17a}

Because of the nature of behavioral interventions, blinding the participants to condition is impossible once the groups start, i.e., they will know if they are in IY or ICDP. Researchers and analysts will not have contact with the families and will not have access to the key file with names and contact information of individual families. All analyses of quantitative data will be conducted using files with participant IDs and intervention condition dummy codes.

### Procedure for unblinding if needed {17b}

Families will know their own condition once the interventions begin; therefore, unblinding is irrelevant.

## Data collection and management

### Plans for assessment and collection of outcomes {18a}

All project data will be stored and analyzed on a platform developed at the University of Oslo (UiT), the Services for Sensitive Data (TSD). TSD is designed to be a secure platform for storing sensitive data and also to process/analyze data using a remote desktop connection.

### Quantitative surveys

#### Families/parents

After families have been recruited, they will receive links to the online surveys. The surveys can be filled out electronically on the participant’s smartphone, desktop/laptop, or tablet. The survey data are delivered via Nettskjema and data are stored in TSD. Data are collected at four measurement points (pre/T1, mid/T2, post/T3, and follow-up/T4). Data from children or parents who withdraws consent will be deleted.

#### Group leaders

Group leaders will be asked to fill out an online survey prior to group start. The group leaders are also requested to fill out weekly checklists regarding their experiences using the intervention which details the content that they cover and use of the MittEcho feedback system. Parent’s attendance is also registered in the checklists. After the group leaders have had experience using the intervention, they will be asked to fill out the group leader questionnaire (GLQ).

#### Teachers

Teachers will receive an invitation to fill out a survey about the child from families participating in the study if the parents have consented. If more than one child in the specific class is participating, the teachers complete one survey for each child. Data is collected at the same measurement points as parent reports (pre/T1, post/T3, and follow-up/T4).

### MFS/MittEcho

MFS data are collected weekly for families in the MFS conditions. The MittEcho app is used to enter the MFS data directly via smartphone or tablet. Data are automatically uploaded to TSD.

### Qualitative interviews

All qualitative interviews will be conducted in-person with parents and children and in-person or over video conference with the group leaders. Data will be collected using smartphones as recording devices that upload the encrypted audio files directly to TSD. The audio recordings will be transcribed in situ on TSD by professional transcribers for analysis.

### Plans to promote participant retention and complete follow-up {18b}

We intend to maintain contact with participating families using the local services. Participants will be compensated for their participation at post- (T3) and follow-up (T4) with gift cards.

## Data management {19}

Data in the PIRM study are considered sensitive and will be gathered and handled following strict guidelines. All data will be stored in a centralized, encrypted database at the University of Oslo which has been developed for the purpose of secure data storage. The database which stores the data for the project is called TSD. It is accessible only to a few personnel who can be given granular access by the project leader to areas that are relevant only to them.

### Quantitative surveys

The quantitative data will be gathered using an online survey developed in Nettskjema. All data are stored on an encrypted, secure database at the University of Oslo. Access to the data files are restricted to project staff and must be approved by the project leaders.

### MFS/MittEcho

MittEcho app data are uploaded directly in encrypted form to TSD on a weekly basis. App data are then directed to a web based MittEcho portal for only approved members of the project. Interventionists in the study apply for membership and gain access to the MittEcho results by secure, two-factor log in. Raw data are stored in TSD until used for analysis.

### Qualitative interviews

The qualitative data will be gathered using an app (Nettskjema Dictaphone App) that automatically uploads the audio files to TSD. The audio files will then be accessible to researchers and transcribers using a remote desktop to access files on TSD.

### Monitoring consort statement

The consort statement is updated throughout the study to track inclusion into, exclusion from, and dropouts from the study. The consort is stored and accessible on TSD. All cases screened are (1) reported to the local coordinator and (2) entered into the “Consort statement” registration by project staff.

#### Drop out during or following randomization

Participants who drop out during or following randomization, i.e., do not wish to continue in the intervention, may be asked why, though they will be reminded that no reason is necessary to drop out. If the participant does not want to participate in the PIRM follow-up, this is registered in the study database.

## Confidentiality {27}

Collected data will be stored on TSD secured storage in files using unique IDs that are linked to the respondents using a matching key that will be stored separately. The matching key will only be accessible to the project coordinators. Project scientists and analysts will only have access to files that use the unique ID. In addition, results of the study will primarily be reported in aggregate. If an individual case or cases are reported (e.g., quotes from qualitative interviews), directly and indirectly identifying information will be omitted. Data will be stored long term in deidentified form.

## Plans for collection, laboratory evaluation, and storage of biological specimens for genetic or molecular analysis in this trial/future use {33}

Biological specimens are not being collected in this study.

## Statistical methods

### Statistical methods for primary and secondary outcomes {20a}

We will conduct analyses in a longitudinal framework, controlling for scores at baseline. For example, to test the primary outcomes of the effectiveness study, we will use linear mixed modeling to assess changes in parenting or child behavior in the different intervention groups while controlling for scores pre-intervention. The analyses will account for independence within the respondents (time as a random effect) as well as group membership, because the randomization to the MFS condition is at the group level. We will also look at interactions between main effects given enough power, for example, between the MFS conditions (factor 2) and the parenting conditions (factor 1).

See the “Outcomes {12}” section for description of qualitative analysis.

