### Intervention description {11a}

The parenting interventions (factor 1) are both implemented as manual-based programs by their official program providers. Both IY and ICDP have extensive documentation which describes the length of the interventions and the contents of intervention meetings. Furthermore, over the course of intervention, data are collected from interventionists that document the content covered for each meeting session with the parents. The IY intervention in the PIRM-study is The School Age Basic Parenting program, which is conducted over 15 weeks with 3-h weekly meetings involving either one or both parents in a group-based setting. This program aims to “strengthen the parent-child interactions and attachment, reduce harsh discipline and foster parents’ ability to promote children’s social, emotional and academic development” (http://www.incredibleyears.com/programs/parent/school-age-basic-curriculum). This again aims to “prevent, reduce, and treat aggression and emotional problems in young children 0 to 12 years old” (http://www.incredibleyears.com/about/incredible-years-series/). The core components include content and process components. The core content components are as follows: positive parental attention, quality time with children, and sensitive responding to support the children’s development and a trusting relationship between parents and children. Development of predictable routines, positive limit setting, and handling of misbehavior are also important components. The content of the meeting is structured in different process core components with the collaborative process as the main element. Other process components are reflection and problem solving, short video vignettes of child-parent interactions, roleplays to practice skills learned, and home activities to enhance and generalize skills and knowledge developed in the group [20].

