### Sample size {14}

#### Quantitative

The sample size for the PIRM study is based on a significance level of *p* = .05 and power *β* = 0.80. The expected effect size is Cohen’s *d* = .30 for the intervention groups based on differences between sum scores. In other words, we wish to detect a relatively small difference between enrollment in either of the parenting groups (factor 1) or in the addition of the MFS (factor 2). Based on this values, our aim is to recruit *N* = 360 families, *n* (IY, w/MFS) = 90, *n* (ICDP, w/MFS) = 90 , *n* (IY, no-MFS) = 90, n (ICDP, no-MFS) = 90. The study is powered to detect a relatively small effect size for main effects of either the parenting factor, IY_tot_ = 180 vs ICDP_tot_ = 180; or the MFS factor, MFS_tot_ = 180 vs no-MFS_tot_ = 180. Interaction effects between factors (e.g., IY w/MFS vs ICDP w/MFS) were not included in the power analysis due to the unknown nature of the main effects. With 6 families in each intervention group, the study would need roughly 5 municipalities to run two intervention groups, twice per year for 3 years.

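### The mixed model names no site-semester effect, although both factors are randomised within site-semesters, and its wording on within-respondent dependence needs correcting

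*Protocol article*

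**What the plan says.** Statistical methods {20a} describes a linear mixed model that controls for the pre-intervention score. On correlation it says: "The analyses will account for independence within the respondents (time as a random effect) as well as group membership". The reason it gives for the group term is that MFS is randomised by group. It also plans to examine the programme by MFS interaction if power allows.

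The randomisation sections describe a blocked design. Sequence generation {16a} states that "each site will conduct both an IY and ICDP parenting group concurrently, so that families can be randomly assigned to either group", and that "Stage 2 randomization is responsible for assigning families at each site to one of the two parenting conditions". The Factor A paragraph under Trial design {8} places this randomisation at the start of each semester. Implementation {16c} assigns MFS so that one of the two groups at each site has it, and reassigns it the next semester.

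Under Sample size {14}, the calculation is "based on a significance level of *p* = .05 and power *β* = 0.80" (the symbol is used for power), with this effect: "The expected effect size is Cohen’s *d* = .30 for the intervention groups based on differences between sum scores". The MFS comparison is given as "the MFS factor, MFS_tot_ = 180 vs no-MFS_tot_ = 180", and the layout as "With 6 families in each intervention group, the study would need roughly 5 municipalities to run two intervention groups, twice per year for 3 years".

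Outcomes {12} wants changes from T1 to T2, T1 to T3 and T3 to T4 compared between the levels of each factor.

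**The concern.** Each site-semester holds one IY and one ICDP group, and exactly one of them has MFS. Both main effects are therefore contrasts within a site-semester. Whatever the two groups share, such as municipality, season and local services, cancels from the difference. A model with a group intercept but no site-semester effect does not know this. It puts the shared variance into the group variance and charges it to both main effects.

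The interaction behaves the other way. A site-semester contains either IY with MFS and ICDP without, or the reverse. The interaction compares these two kinds of site-semester, so block variance belongs in its standard error, and without a block term too little of it is counted.

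The phrase on respondents raises a second issue. Repeated scores from one person are dependent. A random effect of time, standing alone, does not represent that dependence and does not supply the change contrasts in Outcomes {12}. At stake are power for the main effects, the error rate of the interaction test, and the precision claimed for the change contrasts.

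**Working it through.** **The plan's own figure.** For d = 0.30 with SD 1, two-sided 5% (sidedness is not stated) and 80% power, n per level = 2(1.96 + 0.842)²/0.30² = 174.5, so 175 and 350 in total. The planned 180 per level gives power 0.812. N = 360 is reproduced, treating families as independent.

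**Structure.** 5 municipalities x 2 groups x 2 per year x 3 years = 60 groups, in 30 site-semesters. 60 x 6 = 360 families.

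**Assumed inputs.** Total variance 1, block (site-semester) variance vb, group variance vg, remainder ve = 1 - vb - vg. The documents give none of these, so a range is shown.

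**Main effects.**
- Correct SE = sqrt(2(vg + ve/6)/30).
- SE with the block left out = sqrt(2(vb + vg + ve/6)/30).
- Actual type I error = 2[1 - Φ(1.96 x ratio of the two)].
- Power without the block = Φ((0.30 - 1.96 x SE without)/SE correct).

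Example with vb = 0.05, vg = 0.03, ve = 0.92: correct SE = sqrt(2(0.03 + 0.1533)/30) = 0.1106. Without the block, sqrt(2(0.08 + 0.1533)/30) = 0.1247. The ratio is 1.128, type I error 2.7%, and power 69% instead of 77%.

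**Interaction** (15 site-semesters of each kind, if balanced).
- Correct SE = sqrt((4vb + 2vg + 2ve/6)(2/15)).
- SE without the block = sqrt((2vb + 2vg + 2ve/6)(2/15)).

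With vb = vg = 0.05: correct sqrt(0.60 x 2/15) = 0.283, without the block sqrt(0.50 x 2/15) = 0.258. Type I error = 2[1 - Φ(1.96/1.095)] = 7.4%.

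Range at vg = 0.05:

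| vb | Main SE, correct | Main SE, no block | Ratio | Main type I | Power, block / no block | Interaction SE, correct / no block | Interaction type I |
|---|---|---|---|---|---|---|---|
| 0 | 0.118 | 0.118 | 1.00 | 5.0% | 72% / 72% | 0.236 / 0.236 | 5.0% |
| 0.01 | 0.117 | 0.120 | 1.02 | 4.5% | 72% / 71% | 0.246 / 0.240 | 5.5% |
| 0.02 | 0.117 | 0.1225 | 1.05 | 4.0% | 73% / 70% | 0.256 / 0.245 | 6.0% |
| 0.05 | 0.1155 | 0.129 | 1.12 | 2.8% | 74% / 66% | 0.283 / 0.258 | 7.4% |
| 0.10 | 0.113 | 0.139 | 1.23 | 1.6% | 76% / 59% | 0.323 / 0.279 | 9.1% |

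**The phrase on time, read literally.** The literal model (time effect, group intercept, no respondent term) was simulated with four time points, respondent variance 0.5, group variance 0.05 and 4,000 trials per scenario. For the T1 to T3 treatment-by-time contrast the SE was 1.26 to 1.44 times too large, with type I error 0.4 to 1.3%. The reason is simple: respondent variance should cancel from a change score but stays in the residual. With residual variance 0.45 that gives roughly sqrt((0.50 + 0.45)/0.45) = 1.45. Adding a respondent intercept brought type I error to about 5% (4.9 to 5.4%), except in the scenario where slopes also varied by group (8.0%).

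For the time-averaged main effect with no block variance, the same literal model gave type I error 5.3%.

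**The case against.** The analysis paragraph is short, it introduces the model as an example, and it does not exclude site or semester. An article may leave the full random-effects structure to an analysis plan. That is fair as far as it goes. Here, however, the text lists its dependence terms and justifies the group term by the MFS randomisation, while the block within which both factors are randomised is absent from the list.

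The size is unknown. It is nil at zero block variance, small at 0.01 to 0.02, and adjustment for the T1 score may shrink it. That stands in full. So does the fact that the interaction is conditional on power and lies outside the sample size calculation.

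The phrase on time can be read kindly, as a random time slope within respondent together with a respondent intercept. On that reading there is no error from respondent dependence, only a slip in one word. Outcomes {12} already states the change contrasts, and nothing says that time is excluded as a fixed effect.

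Two stronger readings are tempting, and the document does not support them. A reader might infer that a missing respondent term makes the programme and MFS tests produce too many false positives. It does not for the time-averaged effects: both factors are constant within a group, so the group intercept that the plan keeps already carries respondent dependence in the group means (5.3% above). A reader might also infer a missing family level, because IY meetings are described as "involving either one or both parents in a group-based setting". That describes who attends, not who completes the outcome scales. With one respondent per family, separate family and respondent effects could not be estimated.

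**Conclusion.** The point holds as a correction worth making, not as a finding that every standard error is wrong. Leaving out the site-semester makes both main-effect tests conservative and costs power: about 3 percentage points at block variance 0.02, about 8 at 0.05 and about 16 at 0.10 (59% instead of 76% with group variance 0.05). The interaction test is the only one shown to become anti-conservative through the missing block: 7.4% at block and group variance 0.05, and 9.1% at block 0.10. All of these figures rest on assumed variances, 30 equal site-semesters with groups of six, and normal approximations. The wording on respondents is wrong as printed, but it harms the analysis only if no respondent term is fitted, and then by making the treatment-by-time contrasts conservative. The stated N = 360 is reproduced and is not changed by this point.

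**What to change.** In Statistical methods {20a}:

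- Add a site-semester effect alongside the random intercept for group. It may be random or fixed for the main effects. It must be random for the interaction test, because that contrast lies between blocks and fixed block effects would absorb it.
- Change independence to dependence, and state a respondent random intercept (with a random time slope if wanted) or an unstructured covariance over time.
- Enter time as a fixed categorical factor crossed with each condition, so that the model yields the change contrasts listed in Outcomes {12}.
- Add a family level only if more than one parent per family supplies outcomes.

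A named degrees-of-freedom method and a sensitivity analysis for group leaders who run successive groups are optional. The cost is analysis wording only: site, semester, group and respondent are already known from the randomisation and the data collection, and neither sample size nor conduct changes.

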#### Qualitative interview

Interviews for the parents are conducted after the families are finished with the intervention (T3). Interviews for the group leaders are conducted after they have led at least one group to completion (T3). Interviews for the children are conducted after their parents have completed the group (T3 or later).

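### The mixed model names only respondent and parenting group, so the IY-versus-ICDP standard error may be wrong in either direction: site-semester is left out, and leader differences are dealt with for MFS only

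*Protocol article*

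**What the plan says.** Statistical methods for primary and secondary outcomes {20a} describes a linear mixed model adjusted for baseline score. It accounts for repeated measures on the respondent "as well as group membership, because the randomization to the MFS condition is at the group level". No other cluster is named.

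Sequence generation {16a} and Implementation {16c} say that each site runs one IY and one ICDP group at the same time. Families are randomised between the two, and one of the two groups is assigned to MFS. MFS is re-randomised each semester in order to limit "systematic differences that may be introduced by group leaders".

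Sample size {14} is based on "a significance level of *p* = .05 and power *β* = 0.80" and an effect of 0.30 SD, and says "our aim is to recruit *N* = 360 families". With 6 families per group, "the study would need roughly 5 municipalities to run two intervention groups, twice per year for 3 years". The 80% power is claimed for the main effect of either factor.

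**The concern.** The reason given for the group term concerns factor 2 only. Factor 1, IY versus ICDP, is also a main comparison, and two features of the design bear on its standard error.

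First, programme is allocated within site and semester. A site or semester effect shared by both groups cancels from the IY-ICDP difference. If the model has no term for it, that variance goes into the group term and the standard error is too large.

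Second, the protocol itself expects leaders to differ. Leaders are trained by the provider of their programme (Strategies to improve adherence {11c}). Re-randomising MFS can break the link between leader and MFS, but not the link between leader and programme. If a site's IY leaders run several successive IY groups, those groups share a leader effect that does not average out as independent groups would. The standard error is then too small.

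At stake is whether a difference between a few leader teams is reported as a programme effect, or whether similarity of the programmes, which the objectives expect, is reported with the wrong precision.

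**Working it through.** **The plan's own figure.** With a two-sided 5% test, 80% power and d = 0.30, n per arm = 2(1.960 + 0.842)²/0.30² = 175, or 350 in total. With 180 per arm, power is 0.81. The target of 360 is thus reproduced, with families treated as independent. The site arithmetic also fits: 5 sites × 2 groups × 2 per year × 3 years = 60 groups, and 60 × 6 = 360. Each site then runs six successive groups per programme.

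**Set-up.** The total variance is 1, split into site (vs), leader team within site and programme (vt), group (vg) and residual (ve). There are S sites, R groups per team and m = 6 families per group. The protocol gives none of these variances, so all are assumptions; vg = 0.02 throughout unless stated.

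- True variance of the IY-ICDP difference: 2[vt/S + (vg + ve/m)/(SR)]. Site cancels.
- Variance that the group-only model reports, approximately: 2(vs + vt + vg + ve/m)/(SR).
- True SE / model SE = √[(R·vt + vg + ve/m)/(vs + vt + vg + ve/m)].

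The ratio exceeds 1, so that the test is liberal, only if (R − 1)·vt > vs. With six groups per team this is 5·vt > vs.

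**One case in full.** S = 5, R = 6, vt = vg = 0.02, vs = 0, ve = 0.96. True variance = 2[0.004 + 0.18/30] = 0.0200, SE 0.141. Model variance = 2(0.20)/30 = 0.0133, SE 0.115. The ratio is 1.22, so the model SE is 18% too small. A simpler version with residual variance 1 and no separate group variance gives 4/360 + 2(0.02)/5 = 0.0191 against 4/360 + 4(0.02)/60 = 0.0124. That ratio is 1.24 and the model SE is 19% too small (1 − 1/1.24). The type I error is 2[1 − Φ(1.96/1.24)] = 0.114.

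**Type I error by simulation** (20,000 runs per row, balanced, full attendance, teams fixed throughout):

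| Sites × groups per team | vt | vs | True/model SE | Group-only model | Site + group |
|---|---|---|---|---|---|
| 5 × 6 | 0.01 | 0 | 1.12 | 0.077 | 0.078 |
| 5 × 6 | 0.02 | 0 | 1.22 | 0.108 | 0.113 |
| 5 × 6 | 0.05 | 0 | 1.45 | 0.180 | 0.199 |
| 5 × 6 | 0.02 | 0.05 | 1.10 | 0.085 | 0.117 |
| 5 × 6 | 0.01 | 0.10 | 0.91 | 0.044 | 0.083 |
| 5 × 6 | 0 | 0.05 | 0.88 | 0.030 | 0.042 |
| 10 × 3 | 0.02 | 0 | 1.10 | 0.072 | 0.076 |
| 10 × 3 | 0.02 | 0.05 | 0.98 | 0.048 | 0.075 |
| 15 × 2 | 0.02 | 0 | 1.05 | 0.059 | 0.059 |
| 15 × 2 | 0.02 | 0.05 | 0.94 | 0.038 | 0.062 |

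With vt = vs = 0 at 5 sites the group-only test rejects 0.041, slightly under 5%, because the variance estimate is not allowed to fall below the residual part. A t-test on the five site-level IY-ICDP differences (4 df) holds 0.047 to 0.051 in the 5-site settings with vs = 0.

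The last column shows that a site term cures the conservative direction. It also removes the accidental offset that site variance provides, so it does not protect against recurring teams.

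**Power at d = 0.30, 5 sites, fixed teams:**

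| vt | SE | Normal reference | t, 4 df |
|---|---|---|---|
| 0 | 0.111 | 0.77 | 0.54 |
| 0.01 | 0.127 | 0.66 | 0.44 |
| 0.02 | 0.141 | 0.56 | 0.37 |
| 0.05 | 0.178 | 0.39 | 0.26 |

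**The case against.** A reader might infer that the same IY and ICDP teams run successive groups at about five sites, so that the standard error is too small and the 5% test is liberal. The documents do not support that as a flat statement, for three reasons.

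- **Continuity is not stated.** Re-randomising MFS to offset leader differences makes most sense if leaders recur, but nothing says how far they do. Interviewing leaders "after they have led at least one group to completion" is a timing rule that also fits a leader with a single group. Recruitment of group leaders leaves supply to municipalities and implementation teams. The interview target of up to 40 leaders allows for more people than a few fixed teams.
- **Five sites is a planning illustration.** Study setting {9} and Recruitment of municipalities keep site recruitment open. More sites mean fewer groups per team and less inflation.
- **The direction depends on site variance.** Leaving out site works the other way, and the protocol gives no variance from which to judge the net effect. Adjustment for baseline should absorb part of any site difference, which weakens this offset but does not settle its size.

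Two further points carry some weight. The paragraph is a condensed example, and the exact random-effects structure is commonly left to an analysis plan, which is not shown. The word group is also used in Implementation {16c} for a site's continuing IY or ICDP slot, so group membership could be read as that larger unit.

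What remains is that the text gives one reason for clustering, this reason covers one factor, and the only remedy offered for leader differences covers the same factor. The stated power for factor 1 also rests on independent families.

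**Conclusion.** The point holds in conditional form. As written, the model omits the stratum within which both factors are allocated and has no provision for leader differences in the programme comparison. The factor 1 standard error may be too large or too small.

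The upper end, a type I error of about 8%, 11% and 18%, needs full team continuity at 5 sites, six groups per team, zero site variance and a team variance of 0.01, 0.02 and 0.05. At 0.02 the model SE is then 18% to 19% too small. With more sites or appreciable site variance the inflation shrinks, vanishes or reverses: about 5% at 10 sites with team 0.02 and site 0.05, and 3% at 5 sites with site variance 0.05 and no team variance.

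Factor 1 power of 0.80 is not secured under group or team variance. At 5 sites with group variance 0.02 it is 0.77 without a team effect and 0.56 with team variance 0.02, on a normal reference.

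**What to change.** In Statistical methods {20a}, add site-semester to the model alongside the group effect, and give allocation within site and semester as the reason. A random intercept is preferable. Each site-semester has one MFS and one non-MFS group, so the programme-by-MFS product is constant within it. Fixed site-semester effects would absorb the interaction that the section hopes to examine.

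Add a sensitivity analysis for factor 1 with a random intercept for leader team (site × programme, or the actual team where it is known) and small-sample degrees of freedom. Making this the primary model is debatable: on about 4 df, power falls to between 0.26 and 0.54.

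In Sample size {14}, say that the 80% power for factor 1 assumes independent families, and restate it over a range of group and leader-team variance.

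The cost is mainly wording. Leaders already complete surveys and weekly checklists, but the protocol does not describe a link from leader to group for analysis, so this should be confirmed. With few sites the sensitivity interval may be much wider, and the stated factor 1 power becomes less favourable.
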